### Outcomes {12}

#### Primary outcome

The primary element to be investigated in this study is the postoperative volume development of a primarily surgically relieved unilateral CSDH over the course of 3 months postoperatively. For diagnostic purposes and documentation, cranial cross-sectional imaging using native cMRI or CT-scan and subsequent volumetry to visualize the residual hematoma volume in milliliters will be performed at the planned follow-up time points, 1 day postoperatively, 1 week postoperatively, 1 month postoperatively, 2 months postoperatively and 3 months postoperatively. The volumetry will be performed by a radiologist who is not involved in the study. Although he is not informed about the group assignment of each patient, he is not blinded because the group assignment can easily be identified from the radiological evidence of the embolism material in the imaging. All findings are considered in relation to each other and in relation to the initial findings before the operation. The planned examination intervals correspond to the current standard of care for postoperative imaging follow-up after CSDH surgery and reflect the procedure used in comparable studies [27].

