### Sample size {14}

In order to estimate the required sample size, the volume change of a primary operated CSDH under the adjuvant therapy forms to be investigated is analogized with the recurrence rates of primary operated and adjuvant embolized or adjuvant drug-treated CSDH in the literature with regard to the target value defined within the primary objective. For example, the MEMBRANE study, which is currently being recruited, assumes a recurrence rate of 10% when combined surgical and interventional therapy is used [11]. In comparison, the work of Hibahashi et al. [27] puts the recurrence rate of CSDH treated with a combination of surgery and medication at around 2%. Based on this, using the *z*-test for independent samples and an error of the first kind (*α* = 0.05), a sample size of 276 patients (138 per group) is required to achieve a power > 0.8 to detect a difference of 8%.

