## Assignment of interventions: allocation

### Sequence generation {16a}, concealment mechanism {16b}, and implementation {16c}

After the neurosurgeon has checked the inclusion and exclusion criteria, the participants are assigned to treatment with tranexamic acid or embolization in a 1:1 ratio in each study center by means of block randomization after they have given their informed consent and the baseline data have been recorded.

If, in the course of the randomized group allocation, it will be apparent that there are exclusion criteria for inclusion in the test group in the sense of contraindications for the administration of tranexamic acid, or if it will be determine during the procedure that vascular anomalies prevent embolization in patients randomized to the control group, a crossover to the corresponding comparison group is possible after prior further clarification.

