**Fig. 2 Fig2:**
[figure not shown]
Preoperative volume measurement of a right-sided hemispheric chronic subdural hematoma using the CT data set

The following intervention-associated complications will be documented as part of the study:Vascular dissections caused by the guidewireDislocation of embolized materialIschemia caused by vascular occlusion during the interventionInflammation or abscesses at the puncture siteVascular fistula in the area of the puncture siteRetinal blindnessEpidural hematomas after perforation of the meningeal arteryAllergic reactions to the contrast mediumAcute renal failure

The following complications or adverse events associated with the use of tranexamic acid will be documented:Intolerance reactionsPulmonary embolismsVenous thrombosisEpileptic seizuresMyocardial infarctionsCerebral ischemic infarctionsAcute renal failure

All research data, including baseline data (NIHSS, mRS, hematoma volume, patient demographics and characteristics) prior to surgery, will be collected anonymously in an electronic data collection form at each study center. The PI of the trial summarizes these for all centers and exports data for statistical analysis. All investigators will be trained to perform outcome measurements and will be introduced to the data management prior to recruitment of the first patient.

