## Statistical methods

### Statistical methods for primary and secondary outcomes {20a}

The baseline data and outcome parameters are subjected to a simple descriptive data analysis (median, minimum, maximum and standard deviation in each case; mean only for metrically scaled characteristics).

For difference tests for nominal variables (gender, use of anticoagulation prior to surgery, occurrence of complications due to adjuvant therapy procedures, need for revision surgery), the Pearson chi-squared test is used.

For difference tests of ordinally scaled measured variables (NIHSS, mRS) within the respective groups at different points in time (linked samples), the data collected is tested for normal distribution using the Shapiro–Wilk test. In the case of a parametric distribution, the *t*-test is used for linked samples. In the case of a non-parametric distribution, the Wilcoxon test is used for connected samples (for two-group tests).

For the bivariate dependency analysis of the ordinal scaled characteristics between the two groups at the same point in time, the *t*-test for unconnected samples is used for a parametric distribution and the Mann–Whitney *U*-test for a non-parametric distribution after applying the Shapiro–Wilk test.

For metric variables (hematoma volume), which are subject to a normal distribution, the *t*-test for dependent samples is used to analyze the respective groups at different points in time. In the case of a non-parametric distribution, the Wilcox sign-rank test is used for the analysis.

For the bivariate dependency analysis of the metric characteristics between the two groups at the same point in time, after applying the Shapiro–Wilk test, the *t*-test for unrelated samples is used for a parametric distribution and the Mann–Whitney *U*-test for a non-parametric distribution.

In addition, a logistic regression is tested with the revision rate as the dependent variable and the treatment groups and baseline data as independent variables.

Furthermore, a correlation analysis of the relationship between the postoperative volume size and the revision rate as well as the postoperative neurological assessment and the revision rate is performed, in each case for mixed scaling pairs with the chi-squared test. The respective singular correlation analysis is followed by an analysis of the existence of a partial correlation between the two parameters in relation to the revision rate.

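### The between-arm tests of hematoma volume use neither a baseline volume nor centre, and so give away precision the trial could have without extra patients

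*Protocol article*

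**What the plan says.** - **Scans and reference values.** Outcomes {12}, Primary outcome, schedules volumetry at day 1, week 1 and months 1, 2 and 3 after surgery, and adds: "All findings are considered in relation to each other and in relation to the initial findings before the operation".
- **Baseline volume.** Plans for assessment and collection of outcomes {18a} describes the research data as "including baseline data (NIHSS, mRS, hematoma volume, patient demographics and characteristics) prior to surgery". Baseline volume there is the pre-operative one.
- **Between-arm analysis.** Statistical methods {20a} compares metric variables between the arms at a single time point. After a Shapiro–Wilk test, the t-test is chosen ("test for unrelated samples is used for a parametric distribution"), or else the Mann–Whitney U test. Paired tests compare visits within one arm. The only model with baseline data is the logistic regression for revision, which is the secondary outcome.
- **Randomization.** Section {16a}–{16c} allocates patients 1:1 "in each study center by means of block randomization". No analysis in {20a} mentions centre.

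**The concern.** The primary objective compares the arms on the fall in volume after surgery and its time course. Randomization also comes after surgery, so patients enter with differing residual volumes that neither study treatment has caused. If that residual predicts the volume at 3 months, an unadjusted test leaves the predictable part of the variation in its error term. The trial measures volume before surgery and, according to the Primary outcome section, on day 1. Neither value enters a between-arm volume test. The paired tests cannot fill the gap, because each looks at one arm only.

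Blocking within centre balances the arms inside each centre. An analysis without centre does not use that balance: its standard error still contains the between-centre variation that the design has removed from the treatment contrast.

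What is at stake is the width of the interval for the treatment difference. That matters here because Trial design {8} states the aim as equivalence, and a wide interval then supports no conclusion.

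**Working it through.** **1. The plan's own sample size.** Inputs from Sample size {14}: 10% recurrence with embolization ("assumes a recurrence rate of 10% when combined surgical and interventional therapy is used"), 2% with tranexamic acid, α = 0.05, power above 0.8. Sidedness is not stated. For the two-sided z-test with pooled variance, the mean proportion is 0.06 and

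n = [1.960·√(2·0.06·0.94) + 0.8416·√(0.10·0.90 + 0.02·0.98)]² / 0.08² = (0.6583 + 0.2786)² / 0.0064 = 137.2, so 138 per group and 276 in total.

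This matches the stated figure, with power 80.2%. A one-sided test would give 108 per group, so two-sided is used below. The calculation rests on recurrence proportions and supplies no SD or correlation for volume.

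**2. What 138 per group detects on volume, unadjusted.** (1.960 + 0.8416)·√(2/138) = 0.337 SD at 80% power.

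**3. Adjusting for day-1 volume.** Let r be the correlation between day-1 and 3-month volume. It is an assumption, because the protocol gives none. The residual variance is multiplied by 1 − r², the equivalent unadjusted total is 276/(1 − r²), and the detectable difference is 0.337·√(1 − r²).

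| Assumed r | Variance factor | Equivalent unadjusted N | Detectable difference (SD) | Power for 0.337 SD |
|---|---|---|---|---|
| 0.1 | 0.99 | 279 | 0.336 | 80.4% |
| 0.3 | 0.91 | 303 | 0.322 | 83.6% |
| 0.5 | 0.75 | 368 | 0.292 | 89.9% |
| 0.6 | 0.64 | 431 | 0.270 | 93.8% |

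The formula is for a linear model. It does not carry over directly to the Mann–Whitney branch. It applies equally to the pre-operative volume, with that variable's own correlation.

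**4. Adding centre.** Let ICC be the share of volume variance lying between centres (assumed). With the arms balanced within centre, the true variance of the contrast is (1 − ICC) times what the unadjusted test estimates. If centre is ignored, the true α is 2·[1 − Φ(1.960/√(1 − ICC))] and power is Φ(0.8416/√(1 − ICC)). With centre in the model, power is Φ(2.8016/√(1 − ICC) − 1.960).

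| Assumed ICC | True α, centre ignored | Power, centre ignored | Power, centre included |
|---|---|---|---|
| 0.01 | 0.0489 | 80.1% | 80.4% |
| 0.05 | 0.0443 | 80.6% | 82.0% |
| 0.10 | 0.0388 | 81.3% | 84.0% |

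At ICC 0.10 the gain is 84.0 − 81.3 = 2.7 points. Ignoring centre is slightly conservative.

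**5. Is day 1 a usable baseline?** Inclusion is up to 24 h after surgery (Inclusion criteria), tranexamic acid starts within 48 h (Intervention description {11a}), and embolization is within 72 h (Study setting {9}). A day-1 scan can therefore fall after randomization, and possibly after treatment has begun. The follow-up lists in {18a} and {18b} start at week 1, and the legend of Table 1 names no day-1 visit, although its 72-hour postoperative period would cover one. The body of that table is not available to this review.

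**The case against.** The strongest reply is that the prescribed tests are valid. Randomization already allows for chance imbalance in residual volume through the error rate. The gain from adjustment depends on a correlation that nobody has stated and is negligible at r = 0.1. Covariates and centre terms are often left to an analysis plan. The first two statements stand and limit the point to precision. The third does not dispose of it, because {20a} does not leave the choice open: it names the tests.

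Four stronger readings are tempting, and the protocol does not support them.

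- **That day 1 is ignored altogether.** The Primary outcome sentence relates the findings to one another as well as to the pre-operative scan, and the paired tests can include day 1. It is missing only from the between-arm tests.
- **That the outcome is change from the pre-operative scan.** Section {20a} compares volumes at the same visit. If change from that scan were the outcome, with equal SDs and a correlation of 0.3, its variance would be 2(1 − 0.3) = 1.4 times that of the 3-month volume. That 40% increase is conditional on an analysis the protocol does not clearly prescribe.
- **That the primary result is biased or its type I error inflated.** Nothing here shows that, and omitting centre errs in the conservative direction.
- **That patients with a missing scan will simply be dropped.** Section {20c} promises exploratory analyses if much primary endpoint data is missing.

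The objection that day 1 may not precede treatment also stands. It places a condition on the remedy and leaves the point itself intact.

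**Conclusion.** The point holds as one of efficiency. As fixed in {20a}, the between-arm comparison of the primary outcome uses neither a measured baseline volume nor the factor within which randomization is blocked. The resulting tests are valid but less precise than the collected data allow.

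The direction of the loss is certain for any appreciable correlation; its size is not. Over the assumed r of 0.1 to 0.6 it runs from almost nothing to the equivalent of 431 − 276 = 155 patients. The centre component is small throughout. These figures assume a linear model, complete 3-month volumes in 138 patients per arm, and a covariate measured before treatment could affect it.

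**What to change.** Replace the visit-by-visit between-arm tests with one primary analysis: a linear model for 3-month volume with arm, day-1 postoperative volume and centre. Preferably, use a mixed model over week 1 and months 1, 2 and 3 with the same terms plus arm-by-visit terms, reading the 3-month contrast from it. The mixed model also keeps patients who have only some of the scans. Log-transform volume if it is skewed, with a stated rule for volumes of zero, and pool small centres.

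Use day-1 volume as the covariate only if the scan precedes the start of study treatment, preferably randomization. Otherwise use the pre-operative volume. Settle this once for the trial rather than patient by patient, and reconcile the Primary outcome section, which lists a day-1 scan, with {18a}, {18b} and the Table 1 legend, which do not.

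The cost is analysis wording and a check of scan timing, with no added patients. With the 5–8 sites foreseen under Trial status, centre and one covariate take 5 to 8 of 276 − 2 = 274 degrees of freedom in the 3-month linear model.

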#### Secondary outcome

To answer the question specified in the secondary objective, the need for revision surgery on the primary side of patients included in the study is documented depending on the study arm as well as the time interval to the primary procedure.

#### Tertiary outcome

In addition to answering how the postoperative volumes of a primarily surgical relieved CSDH can be influenced by the administration of TXT compared to embolization of the MMA and how high the re-operation rate per treatment arm is, the aim is to show which constellation of symptoms lead to the indication for revision-operation in each case. For this purpose, the hematoma volumes imaged at the follow-up periods will be correlated with the neurological deficits recorded at the follow-up times according to the NIHSS score. Furthermore, the neurological outcome at the end of the study at the 3-month follow-up will be assessed using the modified Rankin Scale and the NIHSS, the results will be compared with the baseline values before surgical hematoma relief.

The National Institutes of Health Stroke Scale (NIHSS) is a scoring system from the field of neurology and was originally used for the early detection and monitoring of stoke progression. The NIHSS score covers the following areas: Level of consciousness, eye movements, integrity of visual fields, facial movements, arm and leg muscle strength, sensation, coordination, speech, language and neglect. Each impairment is rated on an ordinal scale of 0 to 2, 0 to 3, or 0 to 4. The scores are summed up to give a total score of 0 to 42 (the higher the score, the more severe the neurological deficit) [9]. In addition to the diagnosis and follow-up of ischemic strokes, the NIHSS represents an evaluation of the core symptoms of a chronic subdural hematoma that is accepted in the current literature, both in the context of acute diagnosis and in the follow-up situation.

The modified Rankin Scale measures the degree of disability or dependence in the daily activities of people who have suffered a stroke or other causes of neurological disability. The following scaling is used [26].0: No symptoms.1: No relevant impairment. Can carry out everyday activities without restriction despite minor neurological deficits.2: Slight impairment. Can take care of themselves without help but is restricted in everyday life.3: Moderately severe impairment. Needs help in everyday life but can walk without assistance or with aids (walking stick, rollator).4: Severe impairments. Needs help with personal hygiene, cannot walk without assistance.5: Severe disabilities. Bedridden, incontinent, requires constant nursing assistance.

In addition, complications in relation to the interventional procedure and complications and side effects due to the use of tranexamic acid will be documented.

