#### Tertiary objectives

The tertiary objective of this study is the presentation and evaluation of.The constellation of findings that led to the indication for revision surgery in patients included in the study,The neurological outcome of the patients included in the study and assigned to the different treatment arms after a total follow-up period of 3 months,Complications related to the interventional procedure used, andComplications and side effects due to the use of tranexamic acid.

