## Data collection and management

### Plans for assessment and collection of outcomes {18a} and data management {19}

Neurological examination results (NIHSS and mRS) at baseline and at each follow-up time point will be recorded and securely stored by the clinical investigators and supporting study personnel in the form of paper data sheets. The size and extent of the CSDH will be measured using CT or MRI scans without contrast. The volume is measured using a medical image viewing program. (Fig. 2) Follow-up is carried out as shown in Table 1 at 1 week, 1, 2, and 3 months postoperatively after relief of the CSDH during outpatient follow-up visits.

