### Plans to promote participant retention and complete follow‐up {18b}

Participants will be informed about the study’s objective and relevance. The importance of completing the treatment and the follow-up evaluation, both for the study’s quality and for their personal chance to benefit from the therapy, will be emphasized. Participating patients are consciously informed that there are no personal benefits to take part in the study. Nevertheless, it is also explained that there is scientific evidence that patients who are treated as part of a clinical trial can obtain better results than patients who are treated under routine conditions.

Study follow-up is performed at 1 week and 1, 2, and 3 month (± 1 week) after evacuation of the hematoma with an outpatient clinic visit and CT or MRI scans. During these visits, all outcome measurements are performed by one of the researchers. To maximize participant retention, this study follow-up is parallel to the regular follow-up in the outpatient clinic (standard treatment). In addition, appointments for follow-up examinations are made as soon as the patient is discharged from inpatient treatment in order to increase compliance with participation.

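### The method named for showing what led to each revision, a correlation of scheduled-visit volume with scheduled-visit NIHSS, ignores revision status and can use values from the wrong time

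*Protocol article*

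**What the plan says.** All references are to the Protocol article.

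- **Aim.** Tertiary objectives lists "The constellation of findings that led to the indication for revision surgery in patients included in the study". Tertiary outcome puts it at the level of the single patient: "the aim is to show which constellation of symptoms lead to the indication for revision-operation in each case".
- **Method.** The next sentence of Tertiary outcome, introduced as serving that purpose, says that "the hematoma volumes imaged at the follow-up periods will be correlated with the neurological deficits recorded at the follow-up times", with NIHSS as the measure of deficit.
- **When volume is measured.** Primary outcome fixes imaging at "1 day postoperatively, 1 week postoperatively, 1 month postoperatively, 2 months postoperatively and 3 months postoperatively".
- **When neurological status is measured.** Section 18a/19 says: "Neurological examination results (NIHSS and mRS) at baseline and at each follow-up time point will be recorded". It places follow-up "at 1 week, 1, 2, and 3 months postoperatively after relief of the CSDH during outpatient follow-up visits". Section 18b adds: "During these visits, all outcome measurements are performed by one of the researchers".
- **What is recorded about a revision.** Under Secondary outcome, the need for revision "is documented depending on the study arm as well as the time interval to the primary procedure". No volume, NIHSS or symptom at the decision is named there.
- **Related analyses.** Section 20a plans to relate postoperative volume and postoperative neurological assessment to the revision rate. It does not say which time point is used or whether the value must precede the revision.

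**The concern.** The findings that lead to a revision exist when the decision is made. The method named for describing them uses the visit calendar. If a patient deteriorates and is re-operated between the one-month and two-month visits, the one-month values may come from before the deterioration, and the two-month values describe a hematoma that has been evacuated again. Neither is the state that prompted surgery.

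There is a second problem that does not depend on timing. A correlation of volume with NIHSS across patients and visits contains no revision variable. Even with perfectly timed data it would show how volume and deficit go together, not what led to revision in a given patient.

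At stake is one descriptive objective. It still has some weight, because revision is the secondary endpoint and the article's blinding section states that neither patients nor physicians can be blinded. The findings at the decision are what a reader would look for when asking why patients were re-operated. If they are not captured at the event, they may be hard to recover later.

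**Working it through.** **Aim against method.** The aim needs, for each revised patient, the findings at the decision. The method supplies pairs of volume and NIHSS from all patients at fixed visits. It has no revision indicator, no event-time value, and no rule that separates values before a revision from values after it.

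**Expected number of revisions.** Sample size {14} gives 10% (embolization), 2% (tranexamic acid), 138 per group, alpha 0.05 and power above 0.8. The plan's own figure reproduces with a two-sided pooled z-test without continuity correction, where the mean proportion is 0.06:

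n = [1.960·√(2·0.06·0.94) + 0.842·√(0.10·0.90 + 0.02·0.98)]² / 0.08² ≈ (0.658 + 0.279)² / 0.0064 ≈ 137.2, rounded up to 138 per group (276 in total; power 80.2%).

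On those rates, expected revisions are 138 × 0.10 + 138 × 0.02 = 13.8 + 2.8 ≈ 16.6. The objective rests on about 17 cases.

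**Age of the last scheduled scan at revision.** Nominal imaging days are 1, 7, 30, 60 and 90, so the gaps are 6, 23, 30 and 30 days (89 in all). With the one-week windows in the notes to Table 1, the gap between two monthly visits can reach 67 − 23 = 44 days. The article does not say when revisions occur, so two timing patterns were assumed.

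- *Uniform over days 1 to 90.* Mean age = Σg² / (2Σg) = (6² + 23² + 30² + 30²) / (2 × 89) = 2365 / 178 = 13.3 days. Share older than 7 days = (0 + 16 + 23 + 23) / 89 = 62/89 ≈ 70%. Share at most 3 days old = (4 × 3) / 89 ≈ 13%.
- *Early-weighted (exponential, mean 30 days, truncated to days 1 to 90; simulated).* Mean 9.5 days, median 7.4 days. About 52% are older than 7 days and about 23% are at most 3 days old.

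Under both patterns, more than half of the last pre-revision values are over a week old. Every later scheduled value follows the re-operation. Both patterns ignore any clustering of revisions at visits. Clustering would lower these figures.

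**The case against.** The strongest reply is that this is a condensed article. The full protocol and the case report form are not shown, Table 1 is not legible here, and a revision page may exist. Section 22 has adverse events recorded until the end of the study period, and a deterioration leading to re-operation may well fall under its definition. The visits also serve as routine surveillance, so some revisions will be indicated at a visit with current data.

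Much of this stands, and it limits what can be said:

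- A reader might infer that the trial cannot answer the objective at all, or that nearly all revisions fall between visits. The documents do not support either. Revision between visits is an inference from fixed visits and a separately recorded time to revision.
- A reader might infer that the association of volume or deficit with revision will be distorted or even reversed. Section 20a names no time point, so post-revision values may enter, but the text does not say that they will. Choosing the time point can be left to an analysis plan.
- A reader might infer that the trial loses a test of whether the threshold for revision was the same in both arms. That is not a stated objective, and with about 2.8 against 13.8 expected revisions such a comparison would be uninformative anyway.

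The mismatch itself remains. Tertiary outcome does not leave the method open; it names one, and that method does not fit the aim. The adverse event section names neither NIHSS nor volumetry. A revision page, if there is one, would not change the analysis that the article states.

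**Conclusion.** The point holds as a mismatch between a stated aim and the method named for it. The correlation leaves out revision status, and its scheduled values may predate the deterioration or follow the re-operation. It cannot reliably answer the objective for revisions indicated between visits.

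The size is modest: about 17 revisions on the protocol's own rates, with a last scheduled scan about 9.5 to 13 days old on average. Those ages depend on assumed timing. The finding that revision status is missing depends on no assumption. The primary volume endpoint and the secondary revision rate are not touched by this point. It is worth correcting because it is cheap and, per Trial status, recruitment has begun.

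**What to change.** **Tertiary outcome.** Replace the correlation as the method for this objective. For every revision, record NIHSS, mRS, presenting symptoms and the hematoma volume on the scan that indicated the revision. Describe these per revised case, by arm, without a formal comparison.

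**Section 20a.** For the analyses relating volume and neurological status to revision, use only scheduled values taken before any revision, at one common time point for revised and non-revised patients. Exclude post-revision values. Do not put event-time values of revised patients beside scheduled values of the others: that would measure revised patients at their worst, on the findings that prompted surgery, and build in an association. Patients revised before the chosen time point drop out of these analyses, so the time point should be fixed in advance.

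**Cost.** One short CRF page for about 17 patients, and volumetry of scans already taken in clinical care (assuming that a scan precedes each revision). No added visit or scan, and no change in sample size.

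### The listed mRS ends at 5, a living patient, and deaths get no score, so the tertiary 3-month mRS comparison as written covers survivors only

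*Protocol article*

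**What the plan says.** The Tertiary objectives include "The neurological outcome of the patients included in the study and assigned to the different treatment arms" after 3 months. Under Tertiary outcome, "the neurological outcome at the end of the study at the 3-month follow-up will be assessed using the modified Rankin Scale and the NIHSS", and the results are set against the values before surgery.

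The same section defines both instruments.
- **mRS:** the list opens with "The following scaling is used [26].0: No symptoms" and closes with "5: Severe disabilities. Bedridden, incontinent, requires constant nursing assistance". The worst level is a living patient.
- **NIHSS:** "The scores are summed up to give a total score of 0 to 42". It has no value for death either.

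Statistical methods {20a} gives the tests. The between-arm rule begins "For the bivariate dependency analysis of the ordinal scaled characteristics between the two groups at the same point in time" and leads to a t-test or a Mann–Whitney U-test, chosen by Shapiro–Wilk. The within-arm rule begins "For difference tests of ordinally scaled measured variables (NIHSS, mRS) within the respective groups at different points in time (linked samples" and leads to a paired t-test or a Wilcoxon test.

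The section on nonadherence and missing data {20c} offers exploratory analyses if much is missing, and possible multiple imputation of covariates. Death is not mentioned there, in the outcomes, or in the two complication lists.

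**The concern.** A patient who dies before the 3-month visit cannot be placed on a 0–5 list that ends with a living state. All the named tests need a 3-month score, so that patient leaves the comparison. The comparison then no longer covers the patients assigned to each arm, which is what the tertiary objective asks for.

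Deaths are foreseeable, and equal numbers in the two arms cannot be presumed. The article says that incidence rises with age and that the condition can progress to coma. Its complication lists differ by treatment: pulmonary embolism, myocardial infarction and cerebral infarction for tranexamic acid; ischemia and epidural hematoma for embolization. If one treatment led to more deaths among severely disabled patients, its survivors would look better on the mRS because the worst outcomes had been removed.

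**Working it through.** **The plan's own figure.** The only stated number used here is 138 per arm. It comes from recurrence of 10% v 2%, and a two-sided pooled z-test reproduces it:

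n = [1.96·√(2·0.06·0.94) + 0.8416·√(0.10·0.90 + 0.02·0.98)]² / 0.08² = (0.6583 + 0.2786)² / 0.0064 = 137.2, so 138 per arm and 276 in total.

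The mRS does not enter this formula, so nothing below changes N.

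**Assumptions.** The article gives neither a mortality nor an mRS distribution. I assume 30/25/18/14/9/4% for scores 0–5. The mean is 0.25 + 0.36 + 0.42 + 0.36 + 0.20 = 1.59, and 13% of patients score 4–5.

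**Case A: extra deaths come only from patients who would have scored 4–5.** Their mean score is (4·0.09 + 5·0.04)/0.13 = 4.308. Let d be the proportion of extra deaths in one arm, with none in the other.
- Survivors' mean = (1.59 − 4.308d)/(1 − d)
- Mean with death scored 6 = 1.59 + (6 − 4.308)d

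Rejection rates come from simulation: 4,000 trials, 138 per arm, Mann–Whitney at 0.05. The Monte Carlo standard error is about 0.3 to 0.5 percentage points.

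| Extra deaths | Survivors' mean v 1.59 | Shift, deaths dropped | Shift, death = 6 | Rejection, dropped | Rejection, death = 6 |
|---|---|---|---|---|---|
| 2% | 1.535 | −0.055 | +0.034 | about 6% | about 5% |
| 3% | 1.506 | −0.084 | +0.051 | about 7% | about 5% |
| 6.5% | 1.401 | −0.189 | +0.110 | about 14% | about 5% |

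A negative shift makes the arm with more deaths look better. In the last row nearly all rejections with deaths dropped are in that wrong direction.

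**Case B: deaths unrelated to disability.** The survivors' distributions are identical, so dropping deaths causes no shift and the test keeps its level.

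| Deaths | Rejection, dropped | Rejection, death = 6 |
|---|---|---|
| 5% v 2% | about 5% | 7–8% |
| 12% v 3% | about 5% | about 26% |
| 15% v 5% | about 5% | about 31% |

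This is a loss of sensitivity to the mortality difference. It is not bias.

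**Cross-check with another assumed distribution** (20/25/20/15/12/8%, deaths taken from the worst scores first). With 10% v 2% deaths, survivors' means are 1.67 v 1.92; with death = 6 they are 2.10 v 2.00. With 5% v 2%, they are 1.82 v 1.92 and 2.03 v 2.00. With 2% in both arms there is no distortion. The sign reverses in the same way.

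**The case against.** **Exclusion of deaths is nowhere stated.** This is correct. A reader might infer that the trial has decided to leave deaths out of the neurological outcome, and the article does not support that. Exclusion follows only from the closed list and the named tests. A full protocol or analysis plan could say more. But the article fixes the scale itself, so a plan that scored deaths as 6 would contradict it.

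**The missing-data section reaches other analyses too.** It does, but it promises only exploratory work and imputation of covariates. Imputing the outcome would give a dead patient a living patient's score.

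**Deaths will not be lost to the trial.** This stands. Adverse events are recorded whether or not related to treatment, serious ones go to the principal investigator, and a panel monitors them. Deaths by arm should be recoverable. The gap is confined to how they enter the score.

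**The effect may be small.** This stands in part. The 6.5-point scenario means that half of the patients scoring 4–5 die in one arm and none of them in the other. Even then, scoring death as 6 removes the distortion but does not make the test significant. At 2 to 3 points the effect is close to noise. The large contrasts in Case B could be read as evidence of bias, but they show only lost sensitivity.

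**Worst-ranking deaths on the NIHSS.** A reader might extend the remedy this way. It would turn a measure of neurological deficit into a debatable composite, and it does not fit the t-test branch of the plan. I do not ask for it.

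**Conclusion.** The point holds for the mRS as a correction to stated text. Its closed 0–5 list, combined with the named tests, gives a survivors-only comparison at 3 months. Bias towards the arm with more deaths needs two conditions: deaths must differ between arms, and they must fall on the more disabled patients. It would be wrong to conclude that the arm with more deaths will always look better.

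Under the assumed rates, the effect runs from none (equal deaths of the same kind), through 0.05–0.09 points and 6–7% rejection (2 to 3 points of extra deaths), to 0.19 points in the wrong direction and 14% rejection (6.5 points extra, all from scores 4–5). No mortality is given, so the document cannot say where in this range the trial will fall.

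The endpoint is tertiary. The volume outcome, the revision rate and the sample size do not depend on the mRS wording.

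**What to change.** 1. In Tertiary outcome, add a category 6 (dead) to the mRS list.
2. State that every death up to the 3-month visit is scored 6 in the between-arm mRS comparison, and that this comparison uses the rank-based test, so that the step from 5 to 6 carries no assumed distance.
3. Report deaths by arm beside the NIHSS, and label the NIHSS comparison as survivors only.

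The cost is a few lines of text, with no new visits, measurements or patients. The small downside is that the mRS result then combines disability and death, which the report should say. Recruitment is under way, so the rule should be set before outcome data are analysed.
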